## Abstract

**Background:**

General anesthesia usually requires mechanical ventilation, which is traditionally accomplished with constant tidal volumes in volume- or pressure-controlled modes. Experimental studies suggest that the use of variable tidal volumes (variable ventilation) recruits lung tissue, improves pulmonary function and reduces systemic inflammatory response. However, it is currently not known whether patients undergoing open abdominal surgery might benefit from intraoperative variable ventilation.

**Methods/Design:**

The PROtective VARiable ventilation trial (‘PROVAR’) is a single center, randomized controlled trial enrolling 50 patients who are planning for open abdominal surgery expected to last longer than 3 hours. PROVAR compares conventional (non-variable) lung protective ventilation (CV) with variable lung protective ventilation (VV) regarding pulmonary function and inflammatory response. The primary endpoint of the study is the forced vital capacity on the first postoperative day. Secondary endpoints include further lung function tests, plasma cytokine levels, spatial distribution of ventilation assessed by means of electrical impedance tomography and postoperative pulmonary complications.

**Discussion:**

We hypothesize that VV improves lung function and reduces systemic inflammatory response compared to CV in patients receiving mechanical ventilation during general anesthesia for open abdominal surgery longer than 3 hours. PROVAR is the first randomized controlled trial aiming at intra- and postoperative effects of VV on lung function. This study may help to define the role of VV during general anesthesia requiring mechanical ventilation.

**Trial registration:**

Clinicaltrials.gov NCT01683578 (registered on September 3 3012).

## Background

General anesthesia promotes pulmonary atelectasis [1] and this effect is further enhanced during open abdominal surgery [2], mainly due to the use of muscle paralysis. Indeed, with relaxation of the diaphragm, the intra-abdominal pressure is transmitted to the intrathoracic cavity, promoting compression of the lung parenchyma and resulting in more atelectasis. Atelectasis and the decrease in pulmonary gas volume can persist during the postoperative period. It has been shown that forced vital capacity (FVC) and other variables of lung function are reduced for up to three hours postoperatively compared to pre-operative values [3]. It has been shown that noninfectious pulmonary complications like atelectasis or pleural effusions may favor the development of pneumonia [4], and increased bacterial translocation has been found from atelectatic lung regions [5]. The presence of atelectasis may promote the development of ventilator-associated lung injury due to cyclic collapse and re-opening of atelectatic lung regions [6]. Consequently, atelectasis formation is associated with increased length of stay in the recovery room and also with increased admission to the intensive care unit [7,8].

The application of positive end-expiratory airway pressure (PEEP) combined with lung recruitment maneuvers has been shown to reduce atelectasis and improve lung function [9,10]. However, recruitment maneuvers and high levels of PEEP carry the risk of barotrauma and deterioration of hemodynamics, and do not represent standard of practice in general anesthesia.

Recent data suggest that variable ventilation may improve lung function without causing structural damage to the lungs or increasing pulmonary inflammatory response in the experimental [11] and clinical setting [12]. One important mode of action of variable ventilation is the recruitment of previously collapsed lung areas. Variable ventilation is not only able to induce lung recruitment [13], but also to keep alveoli open once they are recruited [14]. This mechanism is of special importance in the presence of low or moderate settings of positive end-expiratory pressure, as planned in the presented trial. Variable ventilation mimics some aspects of the physiological ventilation pattern of healthy, spontaneously breathing individuals, but so far it is not known if variable ventilation is able to improve postoperative pulmonary function and reduce systemic pro-inflammatory response after surgery.

Recently, it has been demonstrated that a lung protective ventilation approach for general anesthesia can improve lung function and decrease postoperative pulmonary complications after open abdominal surgery [9]. The PROtective VARiable ventilation trial (‘PROVAR’) compares conventional (non-variable) lung protective ventilation (CV) and variable lung protective ventilation (VV) regarding pulmonary function and systemic inflammatory response. We hypothesized that VV improves lung function, redistributes ventilation toward gravity-dependent lung areas and reduces systemic inflammatory response compared to CV during controlled mechanical ventilation without spontaneous breathing activity in patients planned for open abdominal surgery expected to be longer than 3 hours.

## Methods/Design

### Objectives and design

PROVAR is an investigator-initiated, single center, randomized controlled, two-arm trial comparing CV and VV in patients receiving mechanical ventilation during general anesthesia for open abdominal surgery.

The study protocol is approved by the institutional review board of the Medical Faculty and the University Hospital Dresden, Germany (EK 174052011) and has been registered at clinicaltrials.gov (NCT01683578). PROVAR is conducted in accordance with the Declaration of Helsinki and the principles of good clinical practice.

PROVAR tests the hypothesis that intraoperative VV is associated with improved pulmonary function and reduced systemic inflammatory response compared to CV in patients planned for open abdominal surgery. Primary endpoint is the FVC on the first postoperative day. Secondary endpoints are plasma concentrations of interleukin (IL)-6, IL-8 and tumor necrosis factor alpha (TNF-α); partial pressure of oxygen in capillary blood (PcO_2_) on the first postoperative day; peak expiratory flow (PEF) on the first postoperative day; forced expiratory volume in the first second (FEV_1_) on the first postoperative day; oxygenation (PaO_2_/F_I_O_2_) during surgery; changes of spatial distribution of ventilation measured by electrical impedance tomography (EIT); amount of atelectasis measured with magnetic resonance imaging (MRI) on the first postoperative day; and occurrence of postoperative pulmonary complications defined by the modified clinical pulmonary infection score (mCPIS) [9]. Figure 1 shows the CONSORT diagram of PROVAR.

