### Screening, enrollment, randomization and blinding

Investigators screen consecutive patients planned for open abdominal surgery with an expected duration >3 h at the University Hospital Dresden, Germany during regular anesthesiological preoperative evaluations. The screening started in September 2012, and a recruitment time of 24 months has been defined based on the incidence of major abdominal surgery and patient characteristics at our hospital. Demographic data of screened patients are recorded regardless of whether they meet the enrollment criteria. Informed consent is obtained from all patients prior to surgery. All screened patients are reviewed with respect to inclusion and exclusion criteria as summarized in Table 1.

**Table 1 T1:** Inclusion and exclusion criteria for the PROVAR trial

**Inclusion**	**Exclusion**
Patients scheduled for elective open abdominal surgery with expected duration >3 h	Chronic lung disease, except COPD GOLD stage I and II and untreated bronchial asthma
ASA class 2 and 3	Body mass index >40
Expected extubation in the OR	Hypersensitivity or allergy against one of the drugs administered during the study or against drugs with similar chemical structure
Informed consent to participate in the study signed by the patient	Participation of the patient in another clinical trial within the last 4 weeks
	History of substance abuse or any other mental status possibly affecting informed consent
	Pregnancy or breastfeeding
	Women in an age range of possible pregnancy if not:
	• Postmenopausal (12 months of amenorrhea or 6 months of amenorrheawith serum FSH >40 lU/ml)
	• Postoperative (6 weeks after bilateral ovariectomy with or without hysterectomy)
	• Regular and correct use of contraceptives with failure rate of <1% per year
	• Sexual inactivity
	• Vasectomy of sexual partner
	Suspected low patient compliance
	Contraindication for MRI exams
	Mechanical ventilation within the last 30 days

ASA, American Society of Anesthesiologists; OR, operating room; COPD, chronic obstructive pulmonary disease; GOLD, global initiative for chronic obstructive lung disease; FSH, follicle-stimulating hormone; MRI, magnetic resonance imaging.

Randomization is performed by random block randomization with fixed 1:1 randomization ratios within blocks of 2 × 10, 3 × 6 and 3 × 4 patients using closed envelopes.

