### Time course of interventions/study protocol

At day 0 (visit 1), informed consent is obtained, demographic data are recorded and spirometry, EIT measurements and capillary blood gas analysis performed to retrieve baseline data. Additionally, potentially fertile female patients are submitted to a pregnancy test.

Visit 2 is performed on the day of surgery. A preoperative MRI of the lungs is performed prior to premedication. Preparation for anesthesia and surgery is done according to standard of care. Anesthesia induction and maintenance is standardized according to the following protocol: all weight-derived calculations are based on ideal body weight defined as 50 or 45.5 (male or female, respectively) + 0.91*(height - 152.4): Anesthesia induction is performed with continuous infusion of 0.5 μg/kg/h remifentanil and a bolus of 1 to 2 mg/kg propofol. Neuromuscular blockade to facilitate endotracheal intubation is achieved by bolus administration of 0.2 mg/kg cisatracurium. Maintenance of anesthesia is monitored by bispectral index (BIS level 40 to 60) and is achieved by continuous infusion of 5 mg/kg/h propofol, 0.2 to 0.3 μg/kg/h remifentanil and 0.09 mg/kg/h cisatracurium. Neuromuscular blockade is checked hourly by muscle relaxometry using the train of four ratio aiming at values of 0 to 1. During induction of anesthesia, an electrolyte solution is administered at a rate of 500 ml/h and reduced thereafter to a maintenance rate of 300 ml/h. Noradrenaline can be infused if necessary to ensure mean arterial blood pressure levels >60 mmHg. After induction and prior to the start of surgery, postinduction measurements are performed and patients are then randomly assigned to mechanical ventilation with CV or VV. EIT measurements and blood plasma samples are obtained postinduction, as well as after surgical wound closure (postclosure) before the end of anesthesia. Arterial blood gases are measured hourly throughout surgery and hemodynamics, as well as spirometric data, are recorded from the monitoring system and the ventilator, respectively. Amounts of infused drugs and fluids, as well as blood loss and urine output, are recorded. Visit 3 takes place on the first postoperative day. Spirometry, lung MRI, EIT, plasma blood sampling and capillary gasometry are performed, and adverse, as well as severe adverse, events (AEs, SAEs) are recorded.

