### Statistics

Sample size calculation was based on a previous study using FVC as a measure of postoperative pulmonary function following general anesthesia [3]. In the present study, effect size was estimated as 1.086, alpha was defined as 0.05 and power as 0.95. Using a two-tailed Mann–Whitney-*U*-test, sample size calculation yielded 25 patients per group. Analysis was performed using GPower (Software Version 3.1.3, University of Düsseldorf, Germany).

Exploratory analysis will include mean and standard deviation for normally distributed variables. Non-normally distributed variables will be expressed by their medians and interquartile ranges. Categorical variables will be expressed as n (%). Parametrical or non-parametrical tests will be used as appropriate to analyze the data. *P* values for multiple comparisons will be adjusted according to the Bonferroni procedure.

In case of loss to follow-up or consent withdrawal from the trial, the causes will be reported. ITT and per protocol (PP) analysis will be conducted. For the intention-to-treat analysis, data will be processed for all trial patients in the groups in which they were randomized. The PP analysis will be performed as a secondary analysis if there are a considerable number of patients who do not receive study therapy or are lost to outcome assessment. Missing data will be handled by means of the last observation carried forward method.

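### The article gives the preoperative FVC no role in the primary comparison; adjusting for it would probably add precision at no cost

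*Protocol article*

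**What the plan says.** All references are to the protocol article.

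- **Endpoint** (Objectives and design): "Primary endpoint is the FVC on the first postoperative day". No change score, percent of baseline or percent predicted is mentioned.
- **Baseline** (Time course of interventions/study protocol, visit 1): "demographic data are recorded and spirometry, EIT measurements and capillary blood gas analysis performed to retrieve baseline data". Randomisation comes later, after induction of anesthesia on the day of surgery, so the visit 1 value cannot be affected by the assigned ventilation mode.
- **Sizing** (Statistics): "effect size was estimated as 1.086, alpha was defined as 0.05 and power as 0.95", then "Using a two-tailed Mann–Whitney-*U*-test, sample size calculation yielded 25 patients per group". No mean difference, SD or measurement scale is given for the 1.086.
- **Analysis** (Statistics): "Parametrical or non-parametrical tests will be used as appropriate to analyze the data". No single test is fixed for the primary endpoint.
- **Covariates** (Discussion, second limitation): thoracic epidural anesthesia will enter the analysis as a covariate. No other covariate is named.
- **Allocation** (Screening, enrollment, randomization and blinding): "random block randomization with fixed 1:1 randomization ratios", in blocks. No stratification is described.

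**The concern.** FVC differs between people for reasons unrelated to ventilation mode, and the eligible population is mixed: both sexes, body mass index up to 40, and COPD GOLD stage I or II allowed. A patient's preoperative FVC is the natural measure of those differences. If it stays out of the primary analysis, the part of the day-1 variance that it could explain remains in the standard error. A chance difference in baseline FVC between two arms of 25 is also carried into the estimate in proportion to r.

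This matters most if the true effect is smaller than the assumed 1.086 SD. At 1.086 SD the trial has power to spare. At about half that effect, whether 50 patients can give a clear answer depends heavily on the residual variance.

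**Working it through.** **Inputs from the article:** effect size d = 1.086, two-sided alpha 0.05, target power 0.95, Mann-Whitney U test, 25 per arm, 1:1 allocation.

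**Assumed:** the correlation r between visit 1 and day-1 FVC. The article gives neither r nor an SD, so results are in units of the between-patient SD of day-1 FVC and are shown for r = 0.3 to 0.9.

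**Step 1. Reproduce the stated sample size.** For a normal parent, the Mann-Whitney test has asymptotic relative efficiency 3/π = 0.955 against the t-test. Power comes from the noncentral t distribution with

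- effective n per arm = 25 × 0.955 = 23.87
- df = 2 × 23.87 − 2 = 45.7
- noncentrality = d × √(effective n / 2) = 1.086 × √(23.87/2) = 3.75

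Power is 0.957 with 25 per arm and 0.949 with 24. So 25 is the smallest size that reaches 0.95, and the stated figure reproduces.

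**Step 2. Unadjusted performance at 25 per arm.**

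- Effect detectable with 80% power: 0.83 SD (Mann-Whitney), 0.81 SD (t-test).
- Mann-Whitney power at a true effect of 0.6 SD: 0.53. At 0.5 SD: 0.39.
- 95% CI half-width for a mean difference: t(0.975, 48) × √(2/25) = 2.011 × 0.283 = 0.57 SD.

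**Step 3. Adjust for visit 1 FVC.** In a linear model the residual variance becomes (1 − r²) times the unadjusted variance, so the residual SD is √(1 − r²). One degree of freedom is lost (df = 47), and the noncentrality is [d/√(1 − r²)] × √(25/2). The half-width is t(0.975, 47) × √(2/25) × √(1 − r²).

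| Assumed r | Residual variance | Detectable effect, 80% power | Power at 0.6 SD | CI half-width |
|---|---|---|---|---|
| 0.3 | 91% | 0.77 SD | 0.59 | 0.54 SD |
| 0.5 | 75% | 0.70 SD | 0.67 | 0.49 SD |
| 0.6 | 64% | 0.65 SD | 0.74 | 0.46 SD |
| 0.8 | 36% | 0.49 SD | 0.93 | 0.34 SD |
| 0.9 | 19% | 0.35 SD | >0.99 | 0.25 SD |

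A second degree of freedom for epidural (df = 46) changes no detectable effect or half-width by more than about 0.001 SD. These figures take no credit for any variance that epidural itself explains.

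**Step 4. Separate the two sources of gain.** Moving from Mann-Whitney to a linear model accounts for 0.83 to 0.81 SD. Only the fall below 0.81 SD is due to the baseline. At r = 0.3 that is 0.81 to 0.77 SD; at r = 0.6 it is 0.81 to 0.65 SD.

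**Step 5. Chance imbalance.** The difference in mean baseline FVC between arms has standard error √(2/25) = 0.28 SD. The probability that it exceeds 0.3 SD in either direction is 2 × [1 − Φ(0.3/0.283)] = 0.29.

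**The case against.** The strongest reply is that silence is being read as a decision. The Mann-Whitney test appears only in the sample-size sentence, and the analysis sentence leaves the test open. A plain Mann-Whitney test cannot take the epidural covariate, so some model is already implied. A full covariate list is often left to an SAP, which is not shown here. All of this stands. A reader might infer that the plan has decided to discard the baseline, but the article does not say so. What remains is that the article does take up covariates, names one, and leaves out the preoperative value of the primary endpoint itself.

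A second reply is that the article does not state the scale of the endpoint or of the 1.086. The Background says the source study found FVC reduced relative to preoperative values, so the effect size could already be baseline-referenced. That also stands. The gains in SD units apply to day-1 FVC as the article defines it, and the scale needs to be stated.

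A third reply is that nothing is invalid. This is correct. Under randomisation the unadjusted comparison is unbiased, its confidence interval already allows for chance imbalance, and the stated sample size reproduces. A reader might infer bias or an underpowered trial; the article's own inputs support neither.

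Finally, it is tempting to say that baseline FVC explains most of the variance. That requires r² > 0.5, that is r above about 0.71, and nothing in the article establishes it.

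**Conclusion.** The point holds as a free improvement. The article describes the primary comparison without a role for the visit 1 FVC, and the likely cost is precision only. At 25 per arm the effect detectable with 80% power would fall from 0.81 SD (t-test) or 0.83 SD (Mann-Whitney) to 0.77, 0.70 or 0.65 SD at r = 0.3, 0.5 or 0.6, and further at higher r.

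The size rests on the assumed r, a roughly linear relation between baseline and day-1 FVC, and approximately normal residuals. The direction is the same at every r examined, but the gain ranges from small to large. If the true effect is near 1.086 SD, the conclusion is unlikely to depend on this choice. If it is nearer 0.6 SD, it may: power is 0.53 with Mann-Whitney, against 0.59 to 0.74 with adjustment at r = 0.3 to 0.6.

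**What to change.** Before unblinding, prespecify the primary analysis as a linear model of day-1 FVC on arm, with visit 1 FVC and thoracic epidural as covariates. Report the adjusted difference with its 95% CI. If residuals are clearly non-normal, use rank ANCOVA with the same covariates; that fallback would not receive the small gain from leaving a rank method. Keep the unadjusted Mann-Whitney test as a supportive analysis, and state the scale on which 1.086 was derived.

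Treat the secondary endpoints that have a pre-randomisation value in the same way: FEV1, PEF and capillary PcO2 (visit 1), MRI atelectasis (preoperative scan) and plasma cytokines (postinduction sample). The EIT endpoint is already defined as a change, so it needs only a statement of the reference time point.

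The cost is wording in the analysis plan. No extra patients, measurements or changes to procedures are needed. Fixing the model now also prevents a later choice among unadjusted, change-score and adjusted results.

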**Figure 1 F1:**
[figure not shown]
**CONSORT diagram for the PROVAR trial.** V_T_, tidal volume; CV V_T,_ coefficient of variation of tidal volume.

### Screening, enrollment, randomization and blinding

Investigators screen consecutive patients planned for open abdominal surgery with an expected duration >3 h at the University Hospital Dresden, Germany during regular anesthesiological preoperative evaluations. The screening started in September 2012, and a recruitment time of 24 months has been defined based on the incidence of major abdominal surgery and patient characteristics at our hospital. Demographic data of screened patients are recorded regardless of whether they meet the enrollment criteria. Informed consent is obtained from all patients prior to surgery. All screened patients are reviewed with respect to inclusion and exclusion criteria as summarized in Table 1.

**Table 1 T1:** Inclusion and exclusion criteria for the PROVAR trial

**Inclusion**	**Exclusion**
Patients scheduled for elective open abdominal surgery with expected duration >3 h	Chronic lung disease, except COPD GOLD stage I and II and untreated bronchial asthma
ASA class 2 and 3	Body mass index >40
Expected extubation in the OR	Hypersensitivity or allergy against one of the drugs administered during the study or against drugs with similar chemical structure
Informed consent to participate in the study signed by the patient	Participation of the patient in another clinical trial within the last 4 weeks
	History of substance abuse or any other mental status possibly affecting informed consent
	Pregnancy or breastfeeding
	Women in an age range of possible pregnancy if not:
	• Postmenopausal (12 months of amenorrhea or 6 months of amenorrheawith serum FSH >40 lU/ml)
	• Postoperative (6 weeks after bilateral ovariectomy with or without hysterectomy)
	• Regular and correct use of contraceptives with failure rate of <1% per year
	• Sexual inactivity
	• Vasectomy of sexual partner
	Suspected low patient compliance
	Contraindication for MRI exams
	Mechanical ventilation within the last 30 days

ASA, American Society of Anesthesiologists; OR, operating room; COPD, chronic obstructive pulmonary disease; GOLD, global initiative for chronic obstructive lung disease; FSH, follicle-stimulating hormone; MRI, magnetic resonance imaging.

Randomization is performed by random block randomization with fixed 1:1 randomization ratios within blocks of 2 × 10, 3 × 6 and 3 × 4 patients using closed envelopes.

Blinding is achieved by means of a modified triple blind design with the patients and postoperative investigators blinded to the treatment and the intraoperative investigator blinded to the pre- and postoperative measurements.

### Intervention

After randomization, patients will be ventilated either with CV or VV, respectively. Both modes are performed with the same ventilator (EVITA XL4Lab, Dräger Medical, Lübeck, Germany) in a volume-controlled mode with a fraction of inspired oxygen (F_I_O_2_) of 0.35, PEEP of 5 cmH_2_O, tidal volumes (V_T_) of 8 ml/kg and an I:E ratio of 1:1. Respiratory rate is adjusted to achieve normocapnia (4.6 to 6.0 kPa). While V_T_ is kept constant during CV, it varies randomly on a breath-by-breath basis during VV. In VV, the mean V_T_ is kept at 8 ml/kg, and the distribution of values follows a Gaussian distribution with coefficient of variation at 30%, as described by our group in detail elsewhere [11]. Such mechanical ventilation mode is accomplished by computer remote control of the ventilator, which is allowed by the manufacturer for clinical use. Table 2 shows the ventilator settings. In case of desaturation (SpO_2_ < 94% for more than one minute) a standardized rescue maneuver is implemented in the protocol. After exclusion of nonventilatory causes, the following interventions will be consecutively performed: 1) a stepwise increase of F_I_O_2_ in steps of 10% up to 100%; 2) a stepwise increase of PEEP in steps of 1 cmH_2_O up to 12 cmH_2_O; and 3) a recruitment maneuver with P_aw_ 40 cmH_2_O for 20s. In case of malfunction or technical problems with the remote computer control during VV, the computer will be disconnected and the ventilator will be switched back to CV. In case of any ventilatory or other medical problems, interventions will be performed based on the discretion of the anesthesiologist in charge of the patient according to clinical standards and will be documented in the case report form accordingly.

**Table 2 T2:** Intraoperative ventilator settings for the PROVAR trial

	**Conventional ventilation**	**Variable ventilation**
**F**_ **I** _**O**_ **2** _	0.35	0.35
**PEEP**	5 cmH_2_O	5 cmH_2_O
**V**_ **T** _	8 ml/kg	Mean value of 8 ml/kg, breath by breath variability with a CV V_T_ of 30%
**RR**	Adjusted according normocapnia (4.6-6.0 kPa)	Adjusted according normocapnia (4.6 to 6.0 kPa)
**I:E**	1:1	1:1
**Flow**	30 L/min, adjusted in case of flow limitation	30 L/min, adjusted in case of flow limitation
**P**_ **max** _	40 cmH_2_O	40 cmH_2_O

F_I_O_2,_ fraction of inspired oxygen; PEEP, positive end-expiratory pressure; V_T_, tidal volume; RR, respiratory rate; I:E, ratio of inspiratory to expiratory time; Flow, air flow; P_max_, maximum of inspiratory pressure; CV V_T_, coefficient of variation of tidal volume.

